### Study objectives

The Teen TB study has three main objectives. The first is to evaluate the relationship between baseline lung imaging (advanced and point of care) and respiratory function in adolescents with TB disease. We aim to test the hypothesis that imaging at the time of diagnosis can predict future lung function. The second objective is to explore the psychosocial experience of adolescents affected by drug-susceptible (DS) and MDR-TB and evaluate if the diagnosis of TB is associated with experiences of stigma. The third objective is to explore how pubertal hormones and viral coinfections (notably cytomegalovirus (CMV)) influence the immune response to *Mtb*. We hypothesise that as adolescents pass through puberty, they generate an increasingly pronounced myeloid inflammatory response to *Mtb*.

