### Study participants

Any adolescent with newly diagnosed pulmonary TB bacteriologically confirmed on sputum (Xpert-positive or culture-positive), with or without HIV coinfection and who are within the first 14 days of treatment, are eligible to participate in this study. Any adolescent exposed in their household to a case of infectious pulmonary TB and who has no symptoms of TB will be considered for the TB-exposed control group. Those with TB disease will be excluded from the study if they have extrapulmonary TB without evidence of pulmonary TB. TB-exposed controls will be excluded if they have previously recovered from TB disease or if asymptomatic TB disease is suspected and/or diagnosed by baseline study investigations. Those suspected of having asymptomatic TB disease will be considered for the TB disease group if they meet the inclusion criteria. Both participants with TB disease and TB exposure will be excluded if they have a severe illness or any condition causing the adolescent to be clinically unstable or requiring intensive care treatment, if pregnant or breast feeding, if known to have diabetes mellitus and if HIV testing is declined with no recent (<12 months) HIV test result available (table 1).

**Table 1 T1:** Inclusion and exclusion criteria for Teen TB

	Inclusion	Exclusion
**Tuberculosis disease**	Any adolescent (10–19 years) who: Has a primary diagnosis of newly diagnosed pulmonary TB bacteriologically confirmed on sputum (Xpert-positive or culture-positive), with or without HIV coinfection Is within the first 14 days since diagnosis and thus 14 days of TB treatment	Extrapulmonary TB without evidence of pulmonary TB Severe illness or any condition causing the adolescent to be clinically unstable or require intensive care treatment Pregnancy or breast feeding (due to exposure to ionising radiation) Diabetes mellitus (due to the potential confounding effects of hyperglycaemia and insulin levels on ^18^F-FDG uptake on PET/CT) Participants declining HIV testing for whom a recent (<12 months) HIV test result is not available

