#### Assessment of study endpoints/primary objectives

Descriptive analysis will be used to characterise the study populations, to compare the TB case and TB-exposed groups and aid in identifying differences between groups with respect to potential confounders. Categorical variables will be expressed as percentages and continuous variables will be expressed as mean±one SD or median with IQR, depending on the distribution of the data.

In those with TB disease, we will categorise disease on CXR as severe and non-severe, using established criteria^29^ and will compare mean z-score of FVC, FEV1 and FEV1/FVC ratio at 2 months and 12 months in those with severe and non-severe disease using a paired sample t-test. We will also evaluate the relationship between severe and non-severe disease on CXR with other measures of functional tests (oscillometry, diffusion capacity, plethysmography, 6MWT and SGRQ). We will perform similar analyses evaluating the ability of ultrasound, CT and ^18^F-FDG PET-CT to predict different measures of lung function at 2 months and 12 months. We will compare the lung function of adolescents with TB disease and those with TB exposure using multivariable logistic regression to adjust for potential confounders and to determine the impact of TB on lung health. From a radiology perspective, we will evaluate the ability of CXR and lung ultrasound to identify findings as seen on CT chest (considered as the imaging ‘gold standard’ for this analysis) using either contingency tests or receiver operating characteristic (ROC) analysis, where appropriate.

Further multivariable analyses will be performed to explore the impact of pubertal hormones on inflammatory cytokines and how the inflammatory cytokines of adolescents with TB disease and TB exposure differ. Immune responses to viral coinfections in participants with TB disease and those with TB exposure will also be compared using regression analysis. Analyses will be performed using STATA (V.17 STATA Corp.).

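### The only viral-coinfection analysis described takes the antiviral response as its outcome, so it does not estimate the influence of CMV on the response to Mtb that objective 3 asks about

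*Protocol article*

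**What the plan says.** Study objectives: "The third objective is to explore how pubertal hormones and viral coinfections (notably cytomegalovirus (CMV)) influence the immune response to" Mtb. The accompanying hypothesis is that, as adolescents pass through puberty, "they generate an increasingly pronounced myeloid inflammatory response to" Mtb.

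Assessment of study endpoints/primary objectives describes three immunology analyses:

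- **Hormones and cytokines:** "Further multivariable analyses will be performed to explore the impact of pubertal hormones on inflammatory cytokines".
- **Cytokines by group:** "how the inflammatory cytokines of adolescents with TB disease and TB exposure differ".
- **Viral coinfection:** "Immune responses to viral coinfections in participants with TB disease and those with TB exposure will also be compared using regression analysis".

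Blood sample collection lists CMV quantitative IgG, RNA sequencing, hormone profiling and a cytokine panel, all at baseline and in both groups. Apart from the HIV test, CMV IgG is the only virus-specific immune measure named.

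On timing, Study participants admits cases who are "within the first 14 days of treatment". Recruitment process aims to approach DS-TB cases before treatment starts, and MDR-TB cases before treatment where possible.

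**The concern.** The objective and the analysis run in different directions. In the objective, CMV is the exposure and the response to Mtb is the outcome. In the analysis, the response to the virus is the outcome and TB disease versus TB exposure is the comparison. Objective 3 is one of three main objectives and CMV is the one virus it singles out. If the sentence is followed literally, the study can report whether CMV antibody levels differ between groups and still say nothing about whether CMV alters the response to Mtb.

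A lesser worry concerns the group comparison of cytokines. Some baseline bloods from cases may be drawn after treatment has begun, so that contrast could mix disease with early treatment response.

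**Working it through.** **Stated figures.** The article gives no figure for objective 3. Its only sample size (Power and sample size) is for spirometry: a difference of 10 points, SD 15, 90% power, alpha 0.05 (taken as two-sided). It reproduces: 2 × (15 × (1.96 + 1.28) / 10)² ≈ 47.3 per group, against the stated 47. The point below does not depend on it.

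**Exposure and outcome side by side.**

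| | Explanatory variable | Outcome |
|---|---|---|
| Objective 3, viral part | CMV | response to Mtb |
| Viral analysis as described | TB group | response to the virus |
| Objective 3, puberty part | pubertal hormones | response to Mtb |
| Hormone analysis as described | pubertal hormones | inflammatory cytokines |

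The puberty rows agree in direction; the viral rows do not.

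**What each regression estimates.** Suppose cytokine = β × IgG + γ × group + error, where β is the effect that objective 3 asks about. Regressing IgG on group estimates mean IgG in cases minus mean IgG in exposed controls. The cytokine does not enter that model, so β cannot appear in its result. Regressing the cytokine on IgG and group estimates β.

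**Simulation.** Assumptions: unit-variance data, 50 per group, IgG independent of TB group, γ = 1, 500 repetitions.

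| True β | IgG on group, mean coefficient | Cytokine on IgG + group, mean IgG coefficient |
|---|---|---|
| 0 | -0.005 | 0.004 |
| 0.5 | -0.005 | 0.504 |
| 1.0 | 0.006 | 1.001 |

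The described comparison gives the same answer whatever β is.

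**Precision of the analysis that is needed.** By Fisher's z (two-sided 0.05, no covariates), the correlation detectable within the 50 cases is tanh((1.96 + 1.28) / √47) = 0.44 at 90% power and tanh((1.96 + 0.84) / √47) = 0.39 at 80%. For a CMV-by-group term on standardised variables, the standard error of the slope difference is about √(2/48) = 0.20, so the difference detectable at 90% power is about 3.24 × 0.204 = 0.66 SD per SD. The within-case slope is feasible for moderate to large effects; the interaction is weak.

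**Timing, illustration only.** Assume the case-versus-exposed gap shrinks linearly, losing a fraction f by day 14, with blood draws uniform over the window. The mean observed gap is then 1 − f/2 of the pre-treatment gap: 95%, 85% and 75% for f = 10%, 30% and 50%. It is 100% if every draw precedes treatment. The article supplies neither f nor the distribution of draws.

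**The case against.** The best defence is that this is one loosely worded sentence in a condensed article. It names neither the outcome nor the predictors of the regression, it belongs to an exploratory component on which the sample size does not rest, and the full protocol or an analysis plan may hold the right model. That is fair as to weight, and it is why the claim should be that no such analysis is described in this article, not that none exists. It does not remove the point. The sentence is not an omitted detail: it states an analysis, and that analysis answers another question. No other sentence supplies the missing one.

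Two stronger readings are tempting and should be resisted.

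- **A reader might infer that the puberty effect also goes unestimated.** The article does plan to "explore the impact of pubertal hormones on inflammatory cytokines", which has the objective's exposure and direction. Nor does the hypothesis require a hormone-by-group interaction. A slope among cases addresses it, and the controls are household-exposed and have an interferon-gamma release assay, so some may be infected. If hormones raise the response in both groups, the interaction could be near zero while the hypothesis is true. The article does not describe the cytokine panel as Mtb-stimulated, but that detail may properly sit elsewhere.
- **A reader might infer that treated cases are compared with untreated controls, with a bias that can be sized.** The article does not state the controls' treatment status. The platform used to find MDR-exposed adolescents belongs to a trial of levofloxacin or placebo. The 14-day limit is the outer edge of eligibility, and the stated aim is to approach cases before treatment. Any shift expressed in SD units would rest wholly on assumed inputs.

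**Conclusion.** The point holds for CMV. The described viral analysis does not match objective 3, and followed as written it yields no estimate of the CMV effect on the response to Mtb. This rests on the text alone; the simulation only illustrates it. It should be corrected, bearing in mind that the component is exploratory.

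Treatment timing is a secondary point. The permitted window allows on-treatment baseline bloods, which bears mainly on the case-versus-exposed cytokine contrast and not on the CMV or hormone slopes. The size and direction of any bias cannot be derived from the document.

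**What to change.** Replace or supplement the viral-coinfection sentence so that CMV is the explanatory variable. Regress the cytokine (or RNA expression) outcomes on CMV IgG level or serostatus, adjusted for TB group, age, sex, HIV status and a pubertal measure (hormone level or Tanner stage). Report the slope within cases, and treat any CMV-by-group term as exploratory. The between-group comparison of antiviral responses can stay as a separate descriptive analysis if it is wanted.

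Secondarily, record days on treatment at the baseline blood draw. Repeat the case-versus-exposed cytokine contrast in a sensitivity analysis limited to cases sampled before or early in treatment, with the cut-off set in advance.

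Cost: analysis wording only for the CMV model, since CMV IgG, cytokines, RNA, hormones, HIV status and Tanner stage are already collected. The timing check needs treatment start and blood-draw dates, which should be obtainable from the clinical history and treating-clinic records. The downsides are wide intervals at 50 per group, widest for the interaction, and a smaller case group in the sensitivity analysis.

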### Data management and confidentiality

At recruitment, each individual will be allocated a unique study number. Personal identifier details will be recorded (eg, name, address and telephone number) but these will thereafter be kept securely and will remain separate from any clinical/epidemiological data, laboratory samples or data resulting from laboratory analysis. These research data will only be linked to the study number. All qualitative data will be audio recorded and transcripts of these recordings anonymised prior to presentation for any audiences outside of the study team. All data (clinical, epidemiological psychosocial and qualitative) will be stored on a secure database at DTTC.

### Patient and public involvement

The development of the protocol, the ethics submission and the strategy for implementation of the study were undertaken in close collaboration with the DTTC Community Advisory Board (CAB). The CAB assists with building and fostering partnerships between researchers and local study communities impacted by TB. The CAB will provide feedback to the research team regarding local issues at clinical research sites and will inform the team of any community concerns that can affect the conduct and implementation of study procedures.

During participant follow-up visits, feedback from adolescents and their caregivers will be used to assess the perceived burden of study interventions and to identify any aspects of their involvement that require improvement or adaptation.

## Ethics and dissemination

The study protocol was approved by the SU Health Research Ethics Committee on 25 February 2020 (N19/10/148). The study will be conducted according to South African and internationally accepted ethical standards, including the Declaration of Helsinki and the South African Good Clinical Practice guidelines. For recruitment, the parents/legal guardians/participants will be required to provide written informed consent in their first language. Adolescents and families will be informed that they are under no obligation to enter the study and that they can withdraw at any time during the study, without having to give a reason.

The study findings will be disseminated through peer-reviewed publications, academic conferences and formal presentations to health professionals and practitioners. Findings will also be communicated to study participants and their caregivers.

## Project status

Recruitment to the study started in November 2020. Follow-up of participants is still ongoing, and the final visit of the last participant with TB disease is planned to be in July 2022. The current protocol is version 1.0.
